## 3. Results

The expected outcomes include improved swallowing function. Patients are supposed to improve swallowing safety and efficiency. The addition of respiratory training to standard intervention is expected to improve coordination between breathing and swallowing, thereby reducing the risk of aspiration and facilitating better management of various food textures. A reduction in the frequency and severity of aspiration events is expected, leading to improved airway protection and a lower incidence of aspiration pneumonia. The respiratory training program is designed to strengthen both inspiratory and expiratory muscles. As a result, significant gains in respiratory muscle strength are expected, as evidenced by increased MIP and MEP values. Patients are also expected to achieve a more effective cough, which is relevant for clearing the airway and reducing the risk of aspiration pneumonia. This improvement should be reflected in higher peak cough flow measurements. Enhancements in swallowing ability are likely to contribute to a better quality of life, including reduced symptoms related to dysphagia and increased comfort during eating and drinking.

The home-based format of the program is expected to improve adherence, promote consistent participation, and achieve better long-term results. By integrating respiratory training with standard therapeutic interventions, the program aims to address both swallowing and respiratory issues more effectively, leading to improved overall rehabilitation outcomes.

The authors will present the study results in a peer-reviewed journal. The procedures and patient involvement at various stages of the study will be illustrated in a flow diagram. The article will highlight the main findings, starting with a table that details the descriptive characteristics of the sample. This will be followed by data comparing baseline outcomes between groups for both primary and secondary measures. Finally, the results of the intervention outcomes will be presented, including within-group and between-group changes, with effect sizes calculated using Cohen’s d.

## 4. Discussion

This study aims to evaluate the impact of a home-based daily intervention focused on inspiratory and expiratory muscle training on swallowing outcomes in patients with chronic stroke. It is hypothesized that patients receiving home-based respiratory training in addition to standard therapy will achieve significant improvements in aspiration risk, respiratory muscle strength, and cough efficacy.

Post-stroke dysphagia can cause health-related problems throughout a patient’s life and is linked to increased healthcare costs [50]. In this context, this study aims to increase the intensity of therapy by using a home-based approach in addition to standard intervention. Implementing home-based interventions allows patients to reduce the frequency of hospital visits. Additionally, with continuous monitoring and personalized care plans, patients with dysphagia often experience better health outcomes and a reduced need for emergency interventions related to respiratory complications [32,50,51].

Previous studies [52,53] have assessed the effects of home-based exercises for patients with dysphagia. Yang et al. [52] conducted a systematic review of home-based telerehabilitation for dysphagia in patients with head and neck cancer. They observed improvements in swallowing safety, adherence to rehabilitation, and quality of life related to swallowing dysfunction. Moreover, the home-based approach demonstrated good efficiency and low costs compared with face-to-face interventions [52]. Additionally, a study involving respiratory muscle training was conducted in patients with Parkinson’s disease presenting with dysphagia using a home-based approach [46]. The authors reported that four-week expiratory muscle strength training significantly reduced dysphagia severity, with a sustained effect after 3 months compared to sham training [53]. In this protocol, we present a home-based approach based on respiratory training for patients with chronic stroke and dysphagia.

Respiratory muscle training has previously shown improvement in respiratory muscle strength, pulmonary function, and functional capacity in early stroke [23,24]. The effects of respiratory muscle training focus on improving swallowing mechanics, which allows for the strengthening of the respiratory muscles and helps generate a more efficient cough, essential for reducing the risk of aspiration pneumonia. Voluntary coughing protects the airway and clears aspiration from the subglottic area [54,55]. Additionally, coordination between breathing and swallowing may be enhanced, minimizing the risk of aspiration during the swallowing-respiration cycle. However, due to the heterogeneity of subjects with dysphagia, the optimal dosage and intensity of exercises for swallowing disorders remain unclear, necessitating further studies to determine these parameters [17].

The studies focused on respiratory training for dysphagia have primarily targeted acute or subacute stroke; more studies on chronic stroke are needed [23,24]. Some authors have reported that swallowing dysfunction persists in patients with chronic stroke [28,29]. However, the improvement of respiratory muscle strength in chronic stroke is not well understood due to the limited studies at this stage of stroke [23,24]. This study focuses on patients with chronic stroke and dysphagia. Combined respiratory training protocols could enhance overall swallowing safety and efficiency in dysphagic post-stroke patients [23,24]. The results of our study will also provide evidence regarding the effects of respiratory intervention in chronic stroke when added to standard intervention. The daily intervention will allow us to increase the intensity of the treatment, overcoming barriers such as therapist or patient availability, extra intervention costs, and patient compliance in the chronic stroke stage.

A study conducted by Krekeler et al. [17] observed that the dosage and intensity in clinical practice are lower compared to research studies. In our study, the respiratory muscle training devices are relatively inexpensive, portable, and easy to use. They require no specialist assistance, making them suitable for use in a home environment. A previous trial focused on supervised, home-based respiratory muscle training showed positive results, achieving a significant improvement in the quality of life of the participants [56]. Our study seeks to increase accessibility to therapy and improve the benefits of the standard intervention by increasing the dosage. Treatment adherence is an important but still unresolved health issue, especially in interventions involving home-based exercises [57]. Increased compliance is linked to an increase in cost-effectiveness. Several systematic reviews have reported that diaries are one of the most used tools to measure adherence in home-based approaches [58,59]. In our study, the patients will complete a diary indicating the repetitions and the symptoms associated with exercise performance.

The proposed home-based respiratory training ensures an individualized program with the appropriate intensity and duration, adapted to the symptoms and baseline values of each participant. Adherence will be facilitated through regular monitoring and program adjustments based on patient progress and feedback. Additionally, the home-based respiratory training will be integrated with other therapeutic interventions for dysphagia, such as dietary modifications, postural adjustments, and traditional swallowing exercises, to achieve comprehensive rehabilitation.

Respiratory training has important clinical applications for managing post-stroke dysphagia. By strengthening both inspiratory and expiratory muscles, this training will improve the coordination between breathing and swallowing, frequently impaired in chronic stroke. Enhanced respiratory muscle strength supports a more effective cough, essential for clearing the airway and preventing aspiration. Furthermore, respiratory training aids in reestablishing better control over the swallowing–respiration cycle, thereby reducing the risk of aspiration pneumonia, a leading cause of morbidity and mortality among stroke survivors. The implementation of respiratory exercises into rehabilitation programs provides a non-invasive, cost-effective approach that can be conducted at home, improving patient adherence and increasing the overall intensity of therapy. This program is expected to improve not only swallowing safety and efficiency but also the quality of life of patients with chronic stroke and dysphagia.

## 5. Conclusions

This study aims to evaluate the effects of home-based daily intervention that focuses on inspiratory and expiratory muscle training on swallowing outcomes in patients with chronic stroke. The results are expected to offer a cost-effective approach, improving accessibility to rehabilitation.

## Figures and Tables

**Figure 1 jcm-13-05547-f001:**
[figure not shown]
Protocol of the home-based respiratory muscle training and standard speech and language interventions.

**Table 1 jcm-13-05547-t001:** Timeline of the study.

	Enrollment and Randomization	Pre-Intervention	Intervention (6 Weeks)	Post-Intervention
Timepoint	First month	Second month	Second and Third month	Fourth month
Enrollment				
▪ Recruitment of patients and verification of inclusion/exclusion criteria.	✓			
▪ Informed consent	✓			
▪ Allocation	✓			
Assessments				
▪ Aspiration risk		✓		✓
▪ Respiratory muscle strength		✓		✓
▪ Voluntary peak cough flow		✓		✓
▪ Functional oral intake level		✓		✓
▪ Quality of life		✓		✓
Interventions				
▪ Experimental Group: Home-based respiratory muscle training + standard speech and language therapy			✓	
▪ Control Group: Standard speech and language therapy			✓	

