## 2. Materials and Methods

### 2.1. Study Design

The research design will be a randomized, single-blind clinical trial. This study will analyze the effect of home-based daily respiratory muscle training in patients with chronic stroke presenting with swallowing dysfunction. This group will be compared with a control group. The timeline of the study is shown in Table 1, including the time point at which the enrollment and randomization procedure, assessments, and intervention will be conducted. 

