### 2.5. Randomization

Participants in this study will be randomly assigned (1:1 ratio) to either an experimental or a control group. The eligibility of participants will be assessed by an independent researcher not involved in the randomization process. The randomization will be performed by a researcher not involved in the study procedure. The randomization sequence will be generated by a computer program (https://www.randomizer.org). The assessment will be carried out by a therapist blinded to the treatment assignments.

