### 2.6. Intervention Protocol

Patients allocated to the experimental group will participate in a 6-week home-based respiratory muscle training program in addition to the standard speech and language intervention. Patients in the control group will receive only the standard intervention. The protocol of both interventions is illustrated in Figure 1. 

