### 2.7. Outcomes

At baseline, clinical and demographic data will be recorded, including age, sex, height, weight, academic studies, the side, site, and the dimension of the cerebral lesion based on the Fugl-Meyer Upper and Lower Extremity scales [38]. Additionally, disease duration and the type of stroke, whether ischemic or hemorrhagic, will be noted. In cases of ischemic stroke, the type of recanalization therapy will be specified. The initial evaluation will be performed once informed consent is obtained. The assessment will be conducted by a blinded therapist with previous experience in treating patients with stroke. 

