#### 2.7.1. Main Outcomes

The main outcomes will include the aspiration risk, the strength of respiratory muscles, and peak cough flow. 

The penetration or aspiration risk will be assessed using the Penetration–Aspiration Scale (PAS) [39]. The PAS is a valid and reliable 8-point scale used during videofluoroscopy assessment. It evaluates the depth of airway invasion, the material remaining after swallowing, and the patient’s response to aspiration. The scores range from 1 (material does not enter the airway) to 8 (material enters the airway, passes below the level of the vocal folds, and no effort is made to eject it). The assessment will be conducted by two experienced researchers, who are blinded to the swallowing performance before and/or after the targeted swallow task. This scale has been reported to be a valid tool for differentiating between normal and abnormal airway protection [39]. 

Respiratory muscle strength will be evaluated using maximal inspiratory pressure (MIP) and maximal expiratory pressure (MEP) measurements [40]. The patients will be evaluated in a sitting position while wearing a nose clip. To evaluate the MIP, the patients will be instructed to exhale air near the residual volume and then inhale through the mouthpiece. To measure MEP, the patients will be asked to inhale air near total lung capacity and then exhale the air through the mouthpiece. Three maneuvers will be performed, ensuring no more than a 20% difference among them [41]. The cut-off values to determine muscle weakness are 62 and 83 cmH_2_O for MIP in females and males, respectively, and 81 and 109 cmH_2_O for MEP in females and males, respectively [42].

Voluntary peak cough flow (L/min) will be evaluated using a peak flow meter (Micro Medical, Cambridge, UK) [43]. This parameter assesses the maximum expiratory flow during a cough to evaluate the efficacy of secretion clearance. The patient will be seated in a chair, will inhale as much air as possible, and then cough as forcefully as possible through the mouthpiece. The maneuver will be performed three times, and the mean of the values will be included in the analysis. Standardized values in healthy adults range between 360 and 400 L/min [44]. An effective cough is associated with having a peak flow rate of over 160 L/min, while a rate below 270 L/min is associated with increased secretion retention and a higher risk of infection [45].

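### Table 1 puts allocation before baseline, so participants can know their arm when they perform the effort-dependent and self-reported baseline measures

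*Protocol article*

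**What the plan says.** Section 2.1 of the protocol article makes Table 1 the study timeline, "including the time point at which the enrollment and randomization procedure, assessments, and intervention will be conducted". The table's time points read "First month Second month Second and Third month Fourth month". Recruitment with the check of entry criteria, consent and allocation are all ticked in the first column, "Enrollment and Randomization", and nowhere else. Aspiration risk, respiratory muscle strength, peak cough flow, oral intake and quality of life are each ticked twice: pre-intervention (second month) and post-intervention (fourth month).

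The text adds one statement on the timing of baseline, in Section 2.7: "The initial evaluation will be performed once informed consent is obtained". It gives no order relative to randomisation.

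On masking, Section 2.1 says "The research design will be a randomized, single-blind clinical trial" and Section 2.5 says "The assessment will be carried out by a therapist blinded to the treatment assignments". Section 2.6 describes no sham: "Patients in the control group will receive only the standard intervention".

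**The concern.** A baseline is safest when it is recorded before anyone can act on the assignment. Here the printed order is the reverse, and participants are not described as blinded. Someone who knows that they will, or will not, receive the added training may try harder or less hard on a maximal-effort test, or answer a quality-of-life questionnaire differently. A blinded assessor cannot remove that, because it arises in the participant's own performance.

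Three of the measured quantities among the main outcomes are of this kind: MIP, MEP and peak cough flow, where the participant must inhale fully and "then cough as forcefully as possible through the mouthpiece". SWAL-QOL, a secondary outcome, is self-reported. Section 3 plans to compare baseline values between groups and to report changes within and between groups with Cohen's d, so the baseline values enter the reported results. A baseline table meant to show comparable groups is also less informative if the values could already reflect the assignment.

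**Working it through.** The point concerns the order of events, so the check is mainly a reading of the sections against each other.

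**1. Order of allocation and baseline.**

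| Source | Allocation | Baseline |
|---|---|---|
| Table 1 | first month only | second month only |
| Section 2.5 | no timing given | no timing given |
| Section 2.7 | not mentioned | after consent |

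Consent is also in the first month, so Section 2.7 is compatible with baseline before or after allocation. It neither contradicts Table 1 nor stands in the way of reordering it.

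**2. Can participants know their arm?** The assessor is blinded (Sections 2.5 and 2.7). No section blinds participants, and without a sham the arm is evident once disclosed. No section withholds the assignment until baseline is complete. The supported statement is therefore that they can know, not that they do.

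**3. Length of the interval.** Taking a month as 365.25/12 = 30.44 days, or 4.35 weeks:
- Months two and three together: 2 × 4.35 = 8.70 weeks.
- The intervention lasts 6 weeks (Section 2.6) and must fit in those two months, so it starts at the latest 8.70 − 6 = 2.70 weeks into month two. Baseline must precede it.
- Longest interval, with allocation on the first day of month one: 4.35 + 2.70 = 7.05, about 7 weeks.
- Shortest interval, with allocation at the end of month one and baseline at the start of month two: near zero.

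**4. How a baseline shift reaches the results.** Let δ be the between-arm difference in mean baseline caused by knowledge of the arm.
- Difference in mean change = (difference in post-treatment means) − (difference in baseline means). The second term contains δ, so the contrast moves by −δ.
- Difference in post-treatment means alone does not contain δ.

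The article gives no value or sign for δ, so no bias can be calculated. The first expression is the arithmetic of any change score and not an estimate of harm.

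**5. Exposure by outcome.**
- MIP, MEP and peak cough flow: exposed through effort.
- SWAL-QOL: exposed through self-report.
- PAS: scored on videofluoroscopy by two blinded researchers (Section 2.7.1), so little exposed.

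**6. Losses in the interval.** A participant who leaves between allocation and baseline is randomised with no baseline record. Each is 1/55 = 1.8% of the planned total. The article gives no basis for the number of such losses.

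**7. Ability to do the tests.** Section 2.4 excludes patients who cannot manage respiratory function testing. In Table 1 the respiratory strength test appears as an outcome only after allocation, although the check of entry criteria is ticked in month one.

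**8. Sample size.** With a difference of 1 PAS point, SD 1.2, two-sided 5% (sidedness assumed) and 80% power, the normal approximation gives 2 × (1.960 + 0.842)² × 1.2² / 1² = 22.6, so 23 per arm and 46 in total. Then 46/0.85 = 54.1, rounded up to 55, which is the stated figure. It does not depend on the order of allocation and baseline.

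**The case against.** The strongest reply is that knowledge of the arm is inferred. The randomising researcher is outside the study procedures, allocation in month one is compatible with disclosure after baseline, and a condensed article may leave the moment of disclosure to the full protocol. This stands as a limit on the claim. It does not remove it: the article prints an explicit order, and that order leaves the question open where the reverse order would close it.

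It is also fair to say that little of the main efficacy case depends on this. The trial is sized on a PAS difference between groups, Section 2.9 names a t-test or Mann–Whitney test and no baseline-adjusted model, and a post-treatment comparison does not carry a baseline shift. This stands too, and it confines the bias to change comparisons in the effort-dependent and self-reported outcomes.

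On losses, someone who leaves on learning their arm lacks a post-treatment value in either order, and the sample size already allows for 15% dropout (0.15 × 55 = 8.25, about 8 participants). Reordering would secure only the baseline value. That allowance protects power, however, and does not make losses equal between arms.

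Some stronger inferences are not supported:
- That eligibility cannot be confirmed before allocation. Section 2.4 sets no entry threshold on PAS, MIP, MEP or cough flow, and Table 1 puts the check of criteria in month one, where ability to perform the tests could be screened.
- That the order blocks stratification on baseline severity. Section 2.5 plans none, so nothing planned is lost.
- That use of MIP and MEP to set training loads worsens the problem. That use is the same in either order.

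**Conclusion.** The point holds in a limited form. Table 1 fixes allocation before baseline, nothing in the article withholds the assignment in between, and participants are not described as blinded. Between-group comparisons of change in MIP, MEP, peak cough flow and SWAL-QOL are therefore open to a bias that the reverse order would avoid. PAS and purely post-treatment comparisons are little affected.

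The interval is between near zero and about 7 weeks, assuming that each participant follows the months in Table 1 and that the full six weeks of intervention fall within months two and three. Neither the size nor the direction of any bias, nor the number of participants lost in the interval, can be derived from the document. A reader might infer that participants do know their arm at baseline or that the results will be biased; the article supports neither. If the assignment is in fact concealed until baseline is complete, what remains is a table that needs correcting and a sentence that needs adding.

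**What to change.** In Table 1, move the allocation tick to after the pre-intervention assessments and rename the first column to match. In Section 2.5, state that the assignment is generated or revealed only once the participant's baseline assessment has been recorded. Section 2.7 can stay as it is.

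This adds no visit, procedure or participant and leaves the sample size of 55 unchanged. It also means that respiratory testing has been attempted before anyone is randomised. The only cost is that the assignment is known slightly later, so scheduling of the device training session and the start of treatment must follow baseline. The change protects the baseline only: with no sham, participants will know their arm at the post-intervention assessment in either order.

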## Data Availability

Not applicable.
